### 2.2. Sample

Our sample consists of patients with a diagnosis of schizophrenia and/or bipolar disorder.

Inclusion criteria:Diagnosis established using ICD-11 clinical criteria (World Health Organization).Aged 18 years or older.Registered on the Patient Portal.With an active prescription for antipsychotic drugs in the MUP.

To participate in the study, patients must have provided informed consent when registering through the Patient Portal, which allows access to their personal data for clinical and scientific purposes.

Exclusion criteria:Aged under 18 years old.Unable to provide consent for medical or legal reasons.Not registered on the Patient Portal.No active prescription for antipsychotic drugs in the MUP.Severe cognitive impairment, as determined by clinical judgment, that prevents the patient from providing informed consent or interacting with digital tools.

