### 2.3. Sample Size Calculation

According to our preliminary data, there are 5458 patients in our hospitals diagnosed with schizophrenia or bipolar disorder and with active antipsychotic dispensing registered in the MUP. Of these, an estimated 90% are registered on the Patient Portal, yielding an initial estimated sample of 4900 people.

Considering that completion of self-administered questionnaires on the Patient Portal is estimated to be around 30%, we expect an approximate sample of 1640 patients to perform the validation calculations for the adherence scales.

The sample size was calculated using G*Power (v3.1) for a one-sample means test (alpha = 0.05, power = 95%, effect size d = 0.5), yielding a minimum of 52 participants. This was based on previous studies exploring the ability of educational interventions to improve medication adherence in the medium term (Loots et al., 2021). Accounting for an anticipated dropout rate of up to 50%, the adjusted minimum is 104. We therefore set a recruitment target of 110 participants, well within the estimated pool of 656 patients expected to present with poor adherence.

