### 2.4. Procedure and Intervention

Project is expected to start in September 2026. We will access the MUP database and cross-reference it with data from the Patient Portal to identify our target sample, that is, those patients who received antipsychotic dispensations who also appear as active users of the Patient Portal. Within the entire sample, we will identify factors associated with adherence issues in the six months prior to the study. The entire sample will then be invited via a message through the Patient Portal to complete the self-report adherence questionnaires.

Finally, the subset of the sample identified with adherence problems will be the target sample for the intervention. Adherence problems to antipsychotics in people with schizophrenia or bipolar disorder are around 40–50%, although the variability in the studies is considerably high (Lingam & Scott, 2002). From the identified pool of patients with poor adherence, a recruitment target of 110 participants has been established. This sample size was determined using G*Power (v3.1) for a one-sample means test (alpha = 0.05, power = 95%, effect size d = 0.5), which requires a minimum of 52 participants (Loots et al., 2021). The final target of 110 accounts for an anticipated dropout rate of up to 50%, ensuring sufficient statistical power despite the high attrition typically observed in this clinical population.

The intervention program will be designed by clinical psychologists with experience in treating patients with bipolar disorder and schizophrenia after a review of the best protocols available in the literature. Presumably, participants will receive psychoeducational materials on the importance of adherence and the potential for mishap management. Tablet handling tips and medication-taking schedules will be reviewed. Participants will also be invited to a telehealth intervention comprising 10 online group psychotherapy sessions delivered via videoconference. These sessions will include cognitive-behavioral measures to manage adherence problems, and adherence will be monitored. Psychotherapy sessions will be led by clinical psychologists, and two sessions will feature testimonials from stabilized patients (See Figure 2).

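### Section 2.3's 1640 expected questionnaire completers should be about 1470 on its own chain, and the poor-adherence pool of 656, apparently built on it, needs restating with a named base

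*Protocol article*

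**What the plan says.** All places are in the protocol article.

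- **Section 2.2** lists as an exclusion "Not registered on the Patient Portal".
- **Section 2.3** starts from 5458 patients with a relevant diagnosis and active antipsychotic dispensing. It puts 90% of them on the Portal, "yielding an initial estimated sample of 4900 people". It then says that "completion of self-administered questionnaires on the Patient Portal is estimated to be around 30" per cent, and concludes: "we expect an approximate sample of 1640 patients to perform the validation calculations for the adherence scales". The recruitment target of 110 is described as "well within the estimated pool of 656 patients expected to present with poor adherence".
- **Section 2.4** defines the target sample as "those patients who received antipsychotic dispensations who also appear as active users of the Patient Portal". It invites that entire sample, through the Portal, to complete the questionnaires. The subset found to have adherence problems becomes the target for the intervention, and a literature rate of 40–50% is given for such problems. From that pool 110 are to be recruited.
- **Section 2.1** says that every patient identified with poor adherence will receive the program.

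**The concern.** Section 2.3 presents its counts as a chain in which each number comes from the one before. The step from 4900 to 1640 does not follow at the stated rate. The size given for the validation objective is therefore wrong as printed, and the pool of 656 appears to carry the same slip forward.

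The base of the pool is also unclear. The figure of 656 suggests that only questionnaire completers can enter the intervention. Section 2.4's wording can be read as drawing on the whole Portal sample, which would give about three times as many candidates. Section 2.1 adds a further mismatch, because a program that recruits 110 cannot be delivered to everyone identified on any of these counts.

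What is at stake is the stated size of the validation sample and a clear description of who is eligible for the pre-post study.

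**Working it through.** **Inputs.** From Section 2.3: 5458 patients, 90% on the Portal, 4900 printed, about 30% completion, 1640 printed, pool of 656 printed, minimum 52, dropout up to 50%, target 110. From Section 2.4: adherence problems in 40–50%.

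**Step 1, Portal sample.** 0.90 × 5458 = 4912. The printed 4900 is this figure rounded.

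**Step 2, completers.**
- On the Portal sample: 0.30 × 4900 = 1470 (0.30 × 4912 = 1474).
- On all patients: 0.30 × 5458 = 1637.
- The printed 1640 matches the second and not the first. The 90% step was skipped.
- People wrongly in the base: 5458 − 4900 = 558. Section 2.2 excludes them, and they cannot receive a Portal questionnaire.
- Overstatement: 1640 − 1470 = 170, and 170/1470 = 11.6%.
- Completion needed to reach 1640 from the Portal sample: 1640/4900 = 33.5%.

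**Step 3, pool.**
- 656/1640 = 0.400 exactly.
- 656/4900 = 0.134, far below 40–50%.
- 656/1470 = 0.446.

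| Who can enter | Base | At 40% | At 50% |
|---|---|---|---|
| Completers, as printed | 1640 | 656 | 820 |
| Completers, corrected | 1470 | 588 | 735 |
| Whole Portal sample | 4900 | 1960 | 2450 |

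At the same rate, the whole-sample pool is 4900/1640 = 2.99 times the printed-completer pool.

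**Step 4, Section 2.1 against recruitment of 110.** Even on the smallest count, 588 − 110 = 478 identified patients would not be enrolled.

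**Step 5, effect on validation precision.** Assume a sensitivity of 0.5 (the widest case) and 40% of completers non-adherent. The 95% half-width is 1.96 × √(0.25/n):
- n = 656: 0.038
- n = 588: 0.040

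**Step 6, effect on the pre-post sample size.** 52/(1 − 0.5) = 104, raised to 110. Neither 1640 nor 656 enters this. The target is 110/588 = 18.7% of the smallest corrected pool and 110/2450 = 4.5% of the largest.

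**The case against.** **The counts are labelled approximate.** Section 2.3 hedges its completion rate and its count, and 33.5% might loosely pass for about 30%. This is fair as to size. But 30% of 5458 gives 1637, so a skipped step explains 1640 better than loose rounding does.

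**656 is not impossible for completers.** It lies inside the corrected completer range of 588–735, at a rate of 44.6%. This stands. A reader might infer that 656 fits no reading of the plan, and that would be too strong. The point is only that 656 is exactly 40% of the wrong 1640, and that the same rate on 1470 gives 588.

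**Section 2.4 does not say that the pool comes from all 4900.** It never multiplies 40–50% by anything, it warns that published rates vary widely, and the sentence on the intervention subset follows the questionnaire invitation. Completers only is therefore a possible reading, and 656 could have been meant as a cautious count of reachable responders. This also stands. The whole-sample pool is one reading of the text and not a stated figure.

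**The entry rule may be elsewhere.** The tool and cut-off that identify poor adherence may be in the full protocol or in the two figures that are not shown. Their absence from a condensed article is not held against the plan here. The wrong completer count, and the conflict between treating everyone identified and recruiting 110, are in the printed text. The second is mainly a matter of wording, since Section 2.4 makes the recruitment clear.

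**Conclusion.** The expected validation sample is overstated by 170 (11.6%): it should be about 1470. The pool of 656 most probably inherits the error. On that inference it becomes about 588 at the same 40%, 588–735 at 40–50% if only completers can enter, or 1960–2450 if the whole Portal sample can. Section 2.1's promise to treat everyone identified disagrees with a recruitment target of 110.

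The consequences are limited. The numbers 52, 104 and 110 do not depend on these counts, 110 fits within every version of the pool, and the half-width for sensitivity widens only from about 3.8 to 4.0 points. A reader might infer that power or recruitment is in doubt, and the documents do not support that.

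A reader might also infer that the pre-post comparison is already biased by regression to the mean, because Section 2.4 says "Within the entire sample, we will identify factors associated with adherence issues in the six months prior to the study" and Section 2.8 uses the six months before the intervention as the comparison period. The documents do not show this. Section 2.4 ties its window to finding associated factors, and the article does not state the tool or window for entry. If dispensing exposure does select patients, and its window overlaps the before period, some rise would be expected without any treatment effect, and a single-arm design could not separate it from benefit. That is a conditional caution. Its size cannot be derived from the article, which gives no correlation between successive exposure periods and no cut-off.

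**What to change.** - **Section 2.3:** change 1640 to about 1470. Replace 656 with the count for the base actually used, and name that base and the rate: 588–735 for questionnaire completers, or 1960–2450 for all Portal-registered patients, at 40–50%.
- **Section 2.4:** name the same base where the intervention subset is introduced.
- **Section 2.1:** say that all enrolled participants receive the same program, with the 110 recruited from the identified pool.
- **If dispensing exposure is the selection tool:** state the selection window and how it relates to the before period in Section 2.8. An earlier, separate window is worth considering but is not a sure remedy, since how much it helps depends on how stable exposure is within patients.

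The cost is wording in three sections and two corrected counts. No new data are needed, and the sample size, recruitment target and analyses do not change.

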### 2.4. Procedure and Intervention

Project is expected to start in September 2026. We will access the MUP database and cross-reference it with data from the Patient Portal to identify our target sample, that is, those patients who received antipsychotic dispensations who also appear as active users of the Patient Portal. Within the entire sample, we will identify factors associated with adherence issues in the six months prior to the study. The entire sample will then be invited via a message through the Patient Portal to complete the self-report adherence questionnaires.

Finally, the subset of the sample identified with adherence problems will be the target sample for the intervention. Adherence problems to antipsychotics in people with schizophrenia or bipolar disorder are around 40–50%, although the variability in the studies is considerably high (Lingam & Scott, 2002). From the identified pool of patients with poor adherence, a recruitment target of 110 participants has been established. This sample size was determined using G*Power (v3.1) for a one-sample means test (alpha = 0.05, power = 95%, effect size d = 0.5), which requires a minimum of 52 participants (Loots et al., 2021). The final target of 110 accounts for an anticipated dropout rate of up to 50%, ensuring sufficient statistical power despite the high attrition typically observed in this clinical population.

The intervention program will be designed by clinical psychologists with experience in treating patients with bipolar disorder and schizophrenia after a review of the best protocols available in the literature. Presumably, participants will receive psychoeducational materials on the importance of adherence and the potential for mishap management. Tablet handling tips and medication-taking schedules will be reviewed. Participants will also be invited to a telehealth intervention comprising 10 online group psychotherapy sessions delivered via videoconference. These sessions will include cognitive-behavioral measures to manage adherence problems, and adherence will be monitored. Psychotherapy sessions will be led by clinical psychologists, and two sessions will feature testimonials from stabilized patients (See Figure 2).

### 2.5. Outcomes

The study’s main outcome is treatment adherence, which was measured through the Morisky-Green 7-item scale (Morisky et al., 1986) and the Haynes-Sackett question (Sackett & Snow, 1979). Additionally, MUP will be used to calculate the percentage of time patients were exposed to antipsychotic treatment over the previous six months, measuring the effectiveness of the intervention. We will also use the MUP to record prescriptions for other medications, including those for general medical conditions.

This study will also gather sociodemographic and clinical data available through the Patient Portal, including sex, age, date of birth, urbanicity, and the presence of physical comorbidities.

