Until relatively recently, the main methods available for measuring treatment adherence were self-report questionnaires, which could be administered either on paper or electronically via platforms such as the Patient Portal. This digital communication platform, operational in some hospitals, allows patients to access appointments and reports and to respond to online questionnaires known as PROMs (patient-reported outcome measures), including medication adherence surveys. A major limitation of these self-report tools is their susceptibility to bias: patients with poor adherence may claim they are taking their treatment when they are not, to avoid intervention from healthcare staff. Also, these questionnaires provide only a cross-sectional picture, whereas continuous long-term monitoring would be more accurate and useful. With the advent of digital electronic prescriptions (Roden et al., 2012), a novel approach to assessing adherence has emerged in several countries, including Spain. In the Community of Madrid, the Single Prescription Module (Módulo Único de Prescripción, MUP) provides access to the patient’s pharmacological history and enables prescription management on this platform. Additionally, this prescription system is interoperable with those of other Autonomous Communities across the country. The MUP allows verification that patients have collected their prescribed medications from the pharmacy, providing an objective method to assess treatment adherence. A critical distinction must be made between self-report adherence measures and dispensing-based data. While self-reports are cost-effective and provide insight into the reasons for non-adherence, they are frequently confounded by recall bias and social desirability, leading to an overestimation of compliance (Nguyen et al., 2014). In contrast, new dispensing data processing tools, such as the PRE2DUP-R package (Tanskanen et al., 2015; Vattulainen et al., 2025), provide an objective, longitudinal record of treatment acquisition. Although dispensing data does not guarantee the actual ingestion of the medication, it serves as a more reliable predictor of clinical relapse than subjective scales in severe mental illness and has been validated both in serum concentration and comprehensive drug treatment interview (Forsman et al., 2018; Krousel-Wood et al., 2015; Taipale et al., 2016).

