### 2.8. Statistical Analysis

Statistical analyses will be performed using R software version 4.5.3 and SPSS software version 30.0, or the latest versions available. All tests will be two-tailed, with 95% confidence intervals, and the level of statistical significance will be set at a *p*-value less than 0.05. The Morisky and Haynes scales (Morisky et al., 1986) will be measured prior to the intervention and again at the end of the sessions, and changes will be analyzed using Pearson’s correlation and simple regression. On the other hand, we will compare the total duration of antipsychotic exposure in the 6 months prior to the intervention with that in the 6 months following the intervention. Similarly, we will compare the average doses to which the sample was exposed before and after the intervention by calculating the recommended daily doses received.

To validate self-report questionnaires, sensitivity, specificity, positive predictive value, and negative predictive value will be calculated using medication collection data from the MUP as the gold standard. ROC curves will be constructed to determine the empirically optimal cut-off for classifying adherence, using the Youden index and reported with 95% confidence intervals, with PRE2DUP-derived antipsychotic exposure as the reference standard.

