To explore factors associated with higher or lower adherence, a logistic regression will be conducted, with adherence as the dependent variable. Adherence will be operationalized using the PRE2DUP method (Tanskanen et al., 2015; Taipale et al., 2016), generating two continuous outcomes: total duration of antipsychotic exposure (days) and average daily dose in DDDs (Tanskanen et al., 2015). These continuous variables will be used as dependent variables in all regression analyses. Furthermore, linear correlations will be performed between adherence levels (using percentage of adherence as a continuous variable) and various potentially implicated factors. To identify factors independently associated with non-adherence, a multivariable logistic regression model will be constructed, incorporating sociodemographic and clinical variables as independent predictors and adjusting for potential confounders (age, sex, diagnosis, comorbidities, and urbanicity). Simple logistic regression and Pearson correlations will be conducted as preliminary exploratory analyses to inform variable selection for the multivariable model. Pre-post changes in adherence outcomes—including PRE2DUP-derived exposure duration and average daily dose in DDDs, as well as self-report scale scores—will be analyzed using linear mixed-effects models, with time (pre- vs. post-intervention) as a fixed effect and subject as a random effect, adjusting for diagnosis, age, and sex.

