### 4.3. Limitations

Several limitations of the ADHERA study must be acknowledged. First, there is a potential selection bias inherent in the recruitment through the Patient Portal; participants who are already digitally literate or more engaged with the health system may be overrepresented, potentially limiting generalizability (Misdrahi et al., 2023). Second, our primary outcome relies on pharmacy dispensing data, which serves as a proxy for adherence but cannot confirm medication ingestion. While it remains a good proxy for objective adherence monitoring (Lam & Fresco, 2015), it cannot account for doses that are collected but not consumed. To address this issue, we will use the PRE2DUP-R R package (Tanskanen et al., 2015; Vattulainen et al., 2025). This method provides an objective approach to medication use and has been validated as a measure of medication use relative to both serum concentrations (Forsman et al., 2018) and a comprehensive drug treatment interview (Taipale et al., 2016). Third, telehealth interventions often experience attrition; although our peer-support component aims to mitigate this, some degree of dropout is expected. Finally, while the MUP system provides objective data, it does not capture medication provided through external samples or private clinical settings not integrated into the public electronic prescription network.

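### Section 2.5 makes self-report scales the main outcome and section 4.3 makes dispensing data the primary outcome; one must be named, with its time point, and the sample size tied to it

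*Protocol article*

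**What the plan says.** Section 2.5 (Outcomes) states that the study's "main outcome is treatment adherence, which was measured through the Morisky-Green 7-item scale" and the Haynes-Sackett question. Its next sentence brings in dispensing data as a measure of how well the programme works: "Additionally, MUP will be used to calculate the percentage of time patients were exposed to antipsychotic treatment over the previous six months, measuring the effectiveness". Section 4.3 (Limitations) reads differently: "our primary outcome relies on pharmacy dispensing data, which serves as a proxy for adherence but cannot confirm medication ingestion".

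Section 2.8 (Statistical Analysis) gives the timing. The two scales "will be measured prior to the intervention and again at the end of the sessions", while antipsychotic exposure is compared between the six months before and the six months after the intervention. The same section lists the pre-post outcomes for the mixed models, "including PRE2DUP-derived exposure duration and average daily dose in DDDs, as well as self-report scale scores", in no order of importance, and sets one two-tailed 0.05 level for all tests.

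Section 1.6 expects adherence to rise and names no measure. Sections 2.3 and 2.4 give the sample size for a means test with d = 0.5 and do not say which outcome d refers to.

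**The concern.** A reader of section 2.5 would judge the intervention on self-report, and a reader of section 4.3 would judge it on dispensing. If the two disagree at the end, the article does not say which one decides.

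Disagreement is plausible. Section 1.2 warns that "patients with poor adherence may claim they are taking their treatment when they are not, to avoid intervention from healthcare staff" and that self-report overestimates compliance. Section 1.5 makes MUP dispensing the gold standard against which these same questionnaires are to be validated, so a self-report primary outcome would rest on an instrument still under test in the same study. The time points also differ, so the two candidates answer different questions: adherence as reported when the sessions finish, and exposure over the following half-year.

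The study has one arm, and the pre-intervention measurement is the only comparator. The identity of the pre-post outcome therefore carries most of the weight of the effectiveness claim.

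**Working it through.** **1. The passages side by side**

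| Section | What it supports |
|---|---|
| 2.5, main outcome | Self-report scales |
| 2.5, following sentence | MUP exposure, added, but said to measure effectiveness |
| 4.3 | Dispensing data as primary |
| 1.5, objective 1 | MUP as gold standard |
| 1.5, objective 3 | Reassessment six months after the intervention |
| 2.8, timing | Scales at end of sessions; MUP over six months before and after |
| 1.6, 2.3, 2.4 | No measure named |
| 2.8, mixed models | All pre-post outcomes, unranked |

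Only the MUP comparison matches the six-month reassessment in objective 3. Most of the text leans towards MUP, but section 2.5 still gives the label of main outcome to the scales.

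**2. The plan's own sample size**

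Inputs from section 2.3: one-sample means test, alpha 0.05, power 95%, d = 0.5. Two-sided testing is from section 2.8.

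- Normal approximation: ((1.960 + 1.645)/0.5)² = 51.98, so 52. This matches the stated minimum.
- Noncentral t: 54 for 95% power; power at n = 52 is 94.3%.
- Dropout of 50%: 52/(1 − 0.5) = 104, as stated; the target is 110.

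The figure reproduces, but only for one test at the full two-sided 0.05. It has no allowance for a second primary outcome.

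**3. False-positive chance if either of the two outcomes could carry the claim**

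For independent tests: 1 − 0.95² = 0.0975. For correlated test statistics (bivariate normal, critical value 1.96, correlation assumed because the article gives none):

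| Correlation | Chance of at least one false positive |
|---|---|
| 0 | 9.75% |
| 0.5 | 9.1% |
| 0.7 | 8.4% |
| 0.9 | 7.0% |

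**4. What two primaries would cost**

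At 0.025 each (Bonferroni), d = 0.5 and 95% power need 63 completers, and 63/0.5 = 126 enrolled, above the target of 110. With 55 completers (half of 110), power per outcome is 91.6%. With one primary outcome, alpha stays at 0.05 and the need is 52 to 54 completers, or 104 to 108 enrolled, within the target.

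**5. Effect of analysing MUP data for all 110 enrolled**

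At n = 110, two-sided 0.05 and 95% power, the detectable effect is d = 0.35. That does not allow for dilution. If half of the participants show no change and the SD is unchanged (assumptions), the mean effect is 0.5 × 0.5 = 0.25, and power at n = 110 is about 74%. At d = 0.30 it is about 88%.

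**The case against.** The strongest reply is that the article, read as a whole, already points to dispensing. Section 2.5 itself assigns the measurement of effectiveness to the MUP, section 1.5 calls it the gold standard, and only the MUP window fits objective 3. This stands in part: the outcome is inconsistently labelled rather than wholly undefined. It does not remove the conflict, because section 2.5 calls the scales the main outcome and section 2.8 tests them pre-post on the same footing.

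Four stronger readings are tempting, and the article does not support them.

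- *That success may be claimed on either outcome.* No section says so. Ranking of secondary outcomes and multiplicity control are often left to an analysis plan, which is not shown here. Such a plan would still have to contradict either section 2.5 or section 4.3.
- *That the error rate is 18.5%.* That is 1 − 0.95⁴ for four independent tests (exposure duration, dose, two scales). The conflict is between two candidates, and all four measure medication-taking in the same patients. Even for four, the figure falls to 9.4% at a correlation of 0.9.
- *That self-report is lost for everyone who drops out.* Section 2.3 says only "Accounting for an anticipated dropout rate of up to 50%, the adjusted minimum is 104" and does not define dropout. Section 2.4 sends the questionnaires through the Patient Portal, so a person who misses sessions could still answer.
- *That self-report must favour the intervention.* Over-reporting would also raise baseline scores and leave less room for improvement. Bias in the change score is plausible, not shown.

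**Conclusion.** The point holds as a contradiction in the current text about which outcome is primary. It matters because the two candidates differ in time point and in susceptibility to bias, and because the sample size is tied to neither.

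If the conflict were used to claim success on either, the false-positive chance would be about 7.0% to 9.75% over assumed correlations from 0.9 to 0. That figure describes what the unresolved text permits, not a rule the article adopts.

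No increase in the recruitment target follows from naming a single primary outcome, provided the planned effect and analysis set are kept. The d = 0.35 at n = 110 should not be presented as a net gain, since dilution could outweigh the larger sample.

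**What to change.** 1. In both section 2.5 and section 4.3, name the same single primary outcome with its time point. The preferable choice is the PRE2DUP/MUP percentage of time exposed to antipsychotics in the six months after the intervention against the six months before, because it matches objective 3 and the gold-standard role in section 1.5.
2. Label the Morisky-Green scale, the Haynes-Sackett question and average dose in DDDs as secondary or supportive.
3. In sections 2.3 and 2.4, state that d = 0.5 refers to the named primary outcome.
4. Analyse MUP data for all enrolled participants whose consent still allows it, whatever their session attendance, and restate power for that analysis set.
5. If two primaries are wanted instead, split alpha and revise the target (126 enrolled at 0.025 each and 50% dropout).

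Steps 1 to 3 are wording only. Step 4 draws on a database the study already uses, but has a real cost: including those who do not attend may dilute the average effect, with power of about 74% at n = 110 in the half-no-change illustration. The change should be made before the planned start in September 2026 and before outcome data are accessed, since after that the choice could no longer be shown to be prespecified.
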